### Objectives

1.2

Aim of this project is to determine whether the use of TR in patients affected by SABI leads to greater (or at least equal) improvement in motor and cognitive function, functional communication, independence in self-care and domestic life, when compared with traditional in-home rehabilitation.

We also aimed to report on the presence of adverse events, feasibility and levels of user satisfaction of SABI patients (living at home) and their caregivers, which are associated to TR, monitoring of patient activities, and health status and telecounseling interventions.

Finally, we aim at evaluating the TR system-related cost-effectiveness, identifying the time necessary to amortize the initial investment for the Information and Communication Technology (ICT) equipment and services set up.

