### Sample size

2.10

Based on the pilot samples during study, we calculated a minimal sample size of 60 participants per group in this study, given a power of >80% to detect an interaction in the 2-way repeated measures, an effect size of 0.61, 4 variables, and 2 repeated measurements.

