### Statistical analyses

2.11

The disability level will be the principal outcome, measured by WHODAS-12 (primary outcomes), and upper limp Fugl-Meyer (secondary outcome). The global cognitive status, assessed by MoCA, will be also a primary outcome. According to the data distribution, parametric or nonparametric statistical tests will be used. In particular, the independent Student *t* test or the Mann–Whitney *U* test will be used to compare the 2 groups, whereas the Student *t* test for unpaired samples or the Wilcoxon signed-rank test will be used to compare the data collected at the first evaluation and the end of the treatment (intragroup analysis). Linear correlation between variables will be computed by Pearson's coefficient or nonparametric Spearman's rank correlation coefficient. Statistical significance will be set at bilateral alpha level of 0.05. HTA assessment: Data will be collected by means of structured checklists, harmonized with all the units, to be administered to all involved actors. Any required data pooling, transformation, averaging, statistics and overall data processing will be performed by Unit 1 and 3 for assessing proper HTA indicators. With respect to cost analysis, specific direct, and indirect costs will be retrieved from each experimental study to allow performing Cost-Effectiveness and Cost-Minimization analysis within HTA3, to be possibly compared with corresponding cost analysis within HTA1. TR will be supported by the adoption of advanced ICT systems, necessary to set up videoconferencing between remote therapists and patient at home, monitor patient health status and activities, and store and process data collected during TR sessions. Monitoring systems will be composed by low-cost nonintrusive devices (such as bracelet or others).

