### Expected outcomes

2.12

1.Patients undergoing TR training will have a greater (or at least the same) improvement in nearly all the motor and cognitive scale scoring administered, with reduced disability (as evaluated by BI and WHODAS2).2.We expect that acceptability and feasibility measures will be significantly higher in the TR group when compared with the conventional treatment, with a concomitant decrease of the caregiver's burden (as per CBI and BDI).3.From the economic point of view, we expect that TR may be a sustainable, low-cost and effective way to deliver rehabilitative interventions.

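### Cost-minimisation is listed beside cost-effectiveness with no condition of equal or non-inferior effect, and the clinical analysis described cannot establish that condition

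*Protocol article*

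**What the plan says.** **Economic analyses.** Section 2.11 of the protocol article states that "specific direct, and indirect costs will be retrieved from each experimental study" in order "to allow performing Cost-Effectiveness and Cost-Minimization analysis within HTA3". The two methods are joined by a plain conjunction. Neither is tied to a clinical result and neither is named as the lead.

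**Economic aim and expectation.** Section 1.2 gives the aim as "we aim at evaluating the TR system-related cost-effectiveness". Section 2.12 adds that "we expect that TR may be a sustainable, low-cost and effective way to deliver rehabilitative interventions". The Discussion expects telerehabilitation (TR) to cost less than usual territorial treatment (UTRT).

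**Clinical analysis.** WHODAS-12 and MoCA are the primary outcomes. The arms are compared by an independent t test or a Mann–Whitney test, and "Statistical significance will be set at bilateral alpha level of 0.05". Section 2.1 says the study is to evaluate whether TR is at least non-inferior, but no margin appears anywhere.

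**Size.** Section 2.10 reports that "we calculated a minimal sample size of 60 participants per group in this study". The target is power above 80% for a group-by-time interaction, and the remaining inputs are listed as "an effect size of 0.61, 4 variables, and 2 repeated measurements". Section 2.2 plans 40 stroke and 40 TBI patients, 20 of each per treatment, which makes 40 per arm.

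**The concern.** A cost-minimisation analysis takes equality of effect as given and then compares costs. No patient outcome enters it. Naming it before the effect is known presupposes the answer to the trial's own clinical question, which the document treats as open: section 1.2 hopes for a greater or at least equal gain, and the Discussion calls earlier data conflicting.

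If TR turned out cheaper and somewhat less effective, the two economic analyses would point in different directions. Cost-minimisation would show a saving, while cost-effectiveness would show a saving obtained at the expense of function. The article does not say which result carries the economic conclusion. A report could therefore present TR as the economical choice when the clinical comparison is merely inconclusive.

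**Working it through.** **Inputs.** Two-sided alpha 0.05 (2.11); effect size 0.61, four variables and power above 80% (2.10); 60 per group (2.10); 40 per arm (2.2). The document gives no margin and does not name the metric of its effect size. I assume a standardised mean difference with SD = 1 and equal arms, and I ignore dropout.

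**1. The plan's own figure.** Per-group size for two means is n = 2 × ((z_alpha + z_power) / d)².
- Alpha 0.05, 80% power, d = 0.61: 2 × ((1.960 + 0.842) / 0.61)² = 42.2, so 43.
- Alpha 0.05/4 for four variables: 2 × ((2.498 + 0.842) / 0.61)² = 59.9, so 60.

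The stated 60 is reproduced if the four variables are read as a Bonferroni split, which the article does not say. Without that split, 60 per group gives about 92% power, which also satisfies the stated condition. On either reading the calculation aims to detect a difference. It does not aim to rule out a loss.

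**2. Precision of the clinical comparison.** The 95% half-width is t(0.975, 2n − 2) × √(2/n).
- n = 40: 1.991 × 0.2236 = 0.445 SD.
- n = 60: 1.980 × 0.1826 = 0.362 SD.

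**3. How often the planned test misses a true loss** (two-sided t test, alpha 0.05, noncentrality d × √(n/2)). The losses are assumed values.

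| True loss | Missed, 40 per arm | Missed, 60 per arm |
|---|---|---|
| 0.3 SD | 74% | 63% |
| 0.4 SD | 58% | 42% |
| 0.5 SD | 40% | 22% |

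For the 0.5 SD row at 40 per arm, noncentrality is 0.5 × √20 = 2.236 and power is 0.598, so 0.402 is missed. At 60 per arm it is 0.5 × √30 = 2.739 and power is 0.775, so 0.225 is missed. A non-significant difference is thus weak evidence of equal effect at either size.

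**4. What a non-inferiority test could deliver**, if one were added (one-sided 0.025, true difference 0, normal approximation): power = Φ(margin / √(2/n) − 1.96). Margins are assumed.

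| Margin | Power, 40 per arm | Power, 60 per arm | Per arm for 80% |
|---|---|---|---|
| 0.61 SD | 78% | 92% | 43 |
| 0.5 SD | 61% | 78% | 63 |
| 0.4 SD | 43% | 59% | 99 |
| 0.3 SD | 27% | 38% | 175 |

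Example: 0.5 / 0.2236 − 1.96 = 0.276, and Φ(0.276) = 0.61.

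**The case against.** **The article is condensed.** The economic analyses sit within items labelled HTA1 and HTA3, which the article does not define, so a fuller economic plan probably exists and may attach the condition. This stands as a limit: the lack of a condition is read from this document's silence. It does not remove the point. Any such condition would need a clinical result to rest on, and the clinical analysis described here, with no margin and only difference tests, does not supply one.

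**Listing both methods can be sensible.** Cost-minimisation is a natural choice if non-inferiority is shown, and cost-effectiveness if it is not. The wording can also be read as describing data collection. Both readings are fair, and they argue for writing the sequence down.

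**Effects are not left out.** A reader might infer that the economic evaluation ignores patient outcomes. It does not: cost-effectiveness is in the same sentence and is the stated aim in section 1.2, and the claim in section 2.12 requires TR to be effective as well as cheap.

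**No decision rule is stated.** A reader might also infer that the plan adopts TR whenever its mean cost is lower. No such rule appears in the document.

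**Sample size is not settled.** Sections 2.2 and 2.10 disagree (40 against 60 per arm), so results are given at both. It would go too far to say that the trial is too small at any margin. At one-sided 0.05 with a margin of 0.61 SD, 34 per arm would suffice for non-inferiority, although two-sided equivalence would need 47. The stated two-sided 0.05 corresponds to 0.025 on one side, where 43 are needed for non-inferiority.

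**Conclusion.** The point holds in a limited form. Cost-minimisation is named without the premise that makes it interpretable, no lead economic analysis is stated, and the clinical tests described cannot supply the premise. At 40 per arm the clinical difference is known only to within about 0.45 SD, and an assumed 0.5 SD loss is missed about 40% of the time. At 60 per arm these become about 0.36 SD and 22%. The figures assume a standardised scale, unadjusted alpha and complete data. They show how uncertain equal effect would remain; they do not predict that TR is worse. The flaw concerns the cost-minimisation component and the order of the economic analyses, not the whole economic evaluation.

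**What to change.** In section 2.11:
- Make the cost-effectiveness analysis the governing economic analysis. Estimate the between-arm differences in cost and in effect jointly from per-patient data, for example by bootstrap, and show the result on a cost-effectiveness plane.
- Drop cost-minimisation, or report it only if non-inferiority on WHODAS-12 and MoCA is shown against a margin stated in advance. Judge this by the confidence interval for the difference, not by a non-significant difference test.
- Reconcile the 40 per arm of section 2.2 with the 60 per group of section 2.10, so that the reader knows what precision the condition rests on.

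In section 2.12, rest the statement about TR being low-cost and effective on the joint result.

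The cost is a change of wording and some extra analysis of data already to be collected, with no added patients for the economic change itself. The downside is that a stand-alone finding of lower cost can no longer serve as the economic conclusion when the clinical result is inconclusive.

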### Expected outcomes

2.12

1.Patients undergoing TR training will have a greater (or at least the same) improvement in nearly all the motor and cognitive scale scoring administered, with reduced disability (as evaluated by BI and WHODAS2).2.We expect that acceptability and feasibility measures will be significantly higher in the TR group when compared with the conventional treatment, with a concomitant decrease of the caregiver's burden (as per CBI and BDI).3.From the economic point of view, we expect that TR may be a sustainable, low-cost and effective way to deliver rehabilitative interventions.

## Discussion

3

Emerging ICT is changing medical and psychological practice by enabling the provision of services across time and distance, yet there are significant concerns about these applications. A recent study by our group have demonstrated that telemedicine can be considered as an important tool in improving health and QoL in the elderly living in nursing homes, and potentially reducing healthcare service access, hospitalization, and costs.^[16]^ It also appears that a telehealth system integrated in a local healthcare service may significantly improve elderly persons’ behavior, and also reduce the caregivers’ burden.^[17]^ Finally, Web-based cognitive rehabilitation has been shown to be useful in improving cognitive performance, besides psychological well-being, in demented individuals living in home care.^[18]^ Specifically, in patients with stroke it has been demonstrated that tele-rehabilitation for motor and higher cortical deficits and in poststroke depression seem to be as or better effective, compared to the “face-to-face” therapies. Although previous data mainly coming from small pilot studies are conflicting, we expect the efficacy of TR is at least noninferior in comparison with the same amount of conventional territorial rehabilitative physical treatments usually delivered to patients suffering from SABI. Exploiting advanced ICT solutions for TR, we also expect a greater improvement in patients’ cognitive and psychological status (as evaluated by specific scales and questionnaires), as well as an improvement in caregivers’ QoL. Taking in account the transfer costs and the time expenditure of conventional rehabilitation, we expect the costs of TR could be inferior in comparison with the costs of UTRT. Moreover, although Chen et al have found no significant differences in abilities of activities of daily living and motor function between conventional and TR, further and more recent studies showed evidence of efficacy in favor of the tele-rehabilitation.^[19–23]^

A recent Cochrane Review found insufficient evidence to reach conclusions about the effectiveness of TR after stroke, as the authors were unable to find any randomized trials that included an evaluation of cost-effectiveness, and to state which intervention approaches was most appropriately adapted to a TR approach.^[17,24–37]^

Our project not only will evaluate the clinical efficacy of TR in a general population (living in 2 different Italian districts), in comparison with conventional neurorehabilitation, but also takes in consideration the cost/efficacy of the system, its feasibility/usability and QoL of the patients and their caregivers.

## Ethics and dissemination

4

### Ethical requirements

4.1

The Principal Investigator (PI) will conduct the study according to the current version of Declaration of Helsinki, the Good Clinical Practice guidelines, and the local regulations.

### Ethics committee

4.2

The PI will obtain ethics committee approval of the protocol informed consent form, and other required study documents before starting the study. After approval, the informed consent will not be altered without the agreement of the relevant ethics committee. It is the responsibility of the PI to ensure that all aspects of institutional review are conducted in accordance with current governmental regulations. Protocol amendments will be subject to the same requirements as the original protocol. A progress report will be submitted to the ethics committee at required intervals and not less than annually. At the completion or termination of the study, the PI will submit a close-out letter to the ethics committee.

### Subject information and consent

4.3

A written informed consent will be obtained from all study participants, according to local regulations. The Investigator will inform the subject that participation to the study is voluntary and that refusal will not lead to loss of any benefit or prejudice the relationship with the physician in any way. Before enrolment into the study, each subject will receive a full explanation of the nature and purpose of the study from the Investigator. A clear Information Sheet covering important aspects in writing will be given to the subject who will read it and have the opportunity to ask any questions whatsoever. The subject will be given adequate time for consideration before he/she is requested to sign the informed consent in duplicate. One of the original copies of the signed informed consent form will be kept by the Investigator.

### Subject confidentiality and data protection

4.4

Before any testing under this protocol, the subjects will also provide all authorizations required by local law (D.Lgs. 196/2003). In agreement with the GCPs, each subject will be identified by a code in an unequivocal manner, which will be the identifier of the subject for the duration of the study.

### Study time table and duration

4.5

–Projected first patient in: December 2018–Projected number of patients: SABI patients–Projected last patient visit: June 2020–Month-duration: 18 months
